## Abstract

**Introduction:**

BRCA1 mutation carriers have a significant lifetime risk of breast cancer, with their primary risk-reduction option being bilateral mastectomy. Preclinical work from our laboratory demonstrated that in BRCA1-deficient breast cells, oestrogen and its metabolites are capable of driving DNA damage and subsequent genomic instability, which are well-defined early events in BRCA1-related cancers. Based on this, we hypothesise that a chemopreventive approach which reduces circulating oestrogen levels may reduce DNA damage and genomic instability, thereby providing an alternative to risk-reducing surgery.

**Methods and analysis:**

12 premenopausal women with pathogenic BRCA1 mutations and no previous risk-reducing surgery will be recruited from family history clinics. Participants will be allocated 1:1 to two arms. All will undergo baseline breast biopsies, blood and urine sampling, and quality of life questionnaires. Group A will receive goserelin 3.6 mg/28 days by subcutaneous injection, plus oral anastrozole 1 mg/day, for 12 weeks. Group B will receive oral tamoxifen 20 mg/day for 12 weeks. Following treatment, both groups will provide repeat biopsies, blood and urine samples, and questionnaires. Following a 1-month washout period, the groups will cross over, group A receiving tamoxifen and group B goserelin and anastrozole for a further 12 weeks. After treatment, biopsies, blood and urine samples, and questionnaires will be repeated. DNA damage will be assessed in core biopsies, while blood and urine samples will be used to measure oestrogen metabolite and DNA adduct levels.

**Ethics and dissemination:**

This study has ethical approval from the Office for Research Ethics Committees Northern Ireland (16/NI/0055) and the Medicines and Healthcare products Regulatory Agency (MHRA) (reference: 32485/0032/001–0001). The investigational medicinal products used in this trial are licensed and in common use, with well-documented safety information. Dissemination of results will be via high-impact journals and relevant national/international conferences. A copy of the results will be offered to the participants and be made available to patient support groups.

**Trial registration number:**

EudraCT: 2016-001087-11; Pre-results.

Strengths and limitations of this studySolid underpinning preclinical data generated within our laboratory.Extensive patient and public involvement in study design and development.Oestrogen and oestrogen metabolite levels assessed using established, highly sensitive mass spectrometry-based methodology.Lack of qualitative intervention to support recruitment and investigate reasons for declining study participation.DNA damage is not currently a validated biomarker for cancer risk.

## Introduction

Women with a germline BRCA1 mutation have up to an 85% lifetime risk of developing breast cancer by age 70, with the majority of these women developing triple negative disease.^1 2^ Intriguingly, a number of retrospective studies, including a large meta-analysis, have demonstrated that risk-reducing oophorectomy significantly reduces the risk of developing breast cancer in this population by up to 50%.^3 4^ In contrast, more recent studies, including a prospective study, contradict this, suggesting some protective effect in BRCA2 but not BRCA1 mutation carriers.^5 6^ However, these studies have limited follow-up (mean follow-up period of 5.6 and 3.2 years respectively), and it is clear from chemoprevention studies carried out in large populations of women at increased risk that a limited chemopreventive effect is seen before 5 years, with significantly greater protective effects seen beyond 10 years.^7^ Furthermore, oophorectomy in a mammary-specific BRCA1 knockout mouse model reduces mammary tumour formation as compared with non-oophorectomised mice.^8^ Taking this together, the evidence suggests that oophorectomy may confer a protective effect in BRCA1 mutation carriers; however, long-term prospective data are required to support this. Currently, risk-reducing mastectomy is the mainstay of preventative treatment offered to BRCA1 mutation carriers, which is effective but carries significant associated costs in terms of physical and psychological morbidity and healthcare spending.^9–11^ Aside from risk-reducing mastectomy, the only other risk-reduction strategy available to these women is chemoprevention.

In the UK, the National Institute for Health and Care Excellence recommends the selective oestrogen receptor modulators (SERMs) tamoxifen and raloxifene for use in women at high risk of developing breast cancer, on the basis that they have been demonstrated to reduce the incidence of oestrogen-receptor positive tumours.^12^ However, evidence on the benefit of tamoxifen as a chemopreventive agent in BRCA1 mutation carriers is conflicting. One small study showed no benefit from tamoxifen in reducing breast cancer risk in BRCA1 mutation carriers, although it has been suggested that tamoxifen use in BRCA1 mutation carriers with breast cancer may reduce the incidence of contralateral tumours.^13 14^ In one case–control study, short-term (2-year) tamoxifen use was as protective for contralateral breast cancer as a longer (5-year) course in BRCA1 and BRCA2 mutation carriers, suggesting some potential chemopreventive efficacy.^15^

However, given that the majority of tumours that develop in BRCA1 mutation carriers are oestrogen receptor (ER)-negative, it seems counterintuitive that SERMs will reduce breast cancer risk, given that no benefit in ER-negative tumours has been shown in the chemoprevention setting with tamoxifen.^12^

Clinical trial data from the  Second International Breast Cancer Intervention Study (IBIS-II) suggest a reduction in breast cancer risk using aromatase inhibitors (AI) in women with increased risk.^16^ However, there is no direct evidence to support a benefit for this approach in BRCA1 mutation carriers.

Clearly oestrogen plays a key role in tumourigenesis in these patients, as tumours develop preferentially in the oestrogen-rich tissues of the breast and ovary.

Preclinical data from our laboratory demonstrate that oestrogen and oestrogen metabolites cause DNA double strand breaks (DSBs) in ER-negative breast cells (normal and cancer cell lines, as well as primary breast progenitor cells isolated from patients), and that BRCA1 is necessary for repression and repair of these DSBs.^17^ The implication of these findings is that in BRCA1-deficient breast cells, exposure to oestrogen and its metabolites is capable of driving genomic instability, a well-defined early event in BRCA1-related cancer development.^18 19^

Taken with evidence from clinical trials, which demonstrate no benefit from SERMs in reducing the incidence of ER-negative tumours, this suggests that SERMs are unlikely to be effective chemopreventive agents in BRCA1 mutation carriers (who are more likely to develop ER-negative tumours). Our data suggest that a chemopreventive approach which lowers circulating oestrogen levels and reduces exposure to oestrogen metabolites within the breast tissue may be more successful by removing this driver of genomic instability. While DNA damage is not at present a validated biomarker of cancer risk in mutation carriers, as described earlier, genomic instability is a well-characterised early hallmark of BRCA1-associated breast tumours. Consistent with this, mice harbouring specific point mutations within BRCA1 affecting its DNA repair function while conserving other protein functions (E3 ligase, transcriptional activity and so on) develop tumours.^20^ This supports the link between DNA damage, genomic instability and tumourigenesis in BRCA1-deficient breast cells.

In postmenopausal women (or premenopausal women who have undergone oophorectomy), the use of an AI may be considered. In premenopausal women with intact ovaries, the induction of reversible ovarian suppression using a luteinising hormone releasing hormone agonist (LHRHa) in combination with an AI, to suppress subsequent aromatase-mediated oestrogen production, may be effective.

Progesterone signalling has also recently been implicated in BRCA1-related tumourigenesis, with the tumour necrosis factor superfamily member RANK (receptor activator of nuclear factor κ B) and its corresponding ligand RANKL (ligand of receptor activator of nuclear factor κ B) functioning as key factors in this pathway and potential targets for chemoprevention.^21^ Importantly, LHRHa suppression of the hypothalamic-pituitary axis will also result in decreased progesterone levels, which will consequently reduce progesterone-dependent RANK/RANKL signalling. Additionally, expression of the progesterone receptor (PR), a critical mediator of the progesterone/RANK/RANKL pathway, is itself driven by oestrogen signalling through the ER. Taken together, the suppression of oestrogen is likely to provide chemopreventive potential, similar to or surpassing that demonstrated through RANK/RANKL suppression.

Although LHRHa, AIs and SERMs are used in breast cancer and fertility treatments, there are no published data in the context of BRCA1-specific chemoprevention where the intention is to prevent ER-negative breast cancer.

It is known that compliance and acceptability of these agents in the adjuvant setting of breast cancer treatment are good, although with a high frequency of side effects.^22^

The compliance of women taking SERMs for chemoprevention is suboptimal, with approximately 40% of women unable to complete 5 years of therapy because of side effects.^23^ Therefore, compliance with LHRHa in combination with an AI in the chemopreventive setting must be assessed and compared with SERM data as an important consideration in the feasibility of use in this context. In line with this, this study aims to inform future tolerability and compliance evaluation in a cohort who may require long durations of treatment and have a long life expectancy.

If the results from this study demonstrate that these treatments are a feasible and tolerable strategy, and that DNA damage is reduced through reduced levels of circulating oestrogen, this would provide data to support the proposed mechanism of oestrogen-driven tumourigenesis in BRCA1 mutation carriers. Furthermore, this may provide evidence to support further studies evaluating the use of this chemopreventive strategy in BRCA1 mutation carriers. Nevertheless, this would require a multicentre international collaborative study, which presents significant challenges. Undoubtedly the treatment regimen proposed within this study has a clear side-effect profile, the tolerability and acceptability of which will be addressed in this study. Currently, a number of groups are investigating inhibition of progesterone and/or RANK/RANKL signalling as an alternative chemopreventive strategy in BRCA1 carriers, which may present a more tolerable approach.^24^ However, a recent study using a well-characterised mouse model of BRCA1-associated breast cancer suggests that oestrogen is the predominant driver of tumourigenesis rather than progesterone.^25^ Given that RANK/RANKL signalling is progesterone-dependent, the efficacy of these progesterone and RANK/RANKL-targeted chemopreventive approaches remains unproven. In light of this, continued exploration of oestrogen suppression in this cohort is justified in order to maximise the repertoire of potential chemopreventive options in this area of unmet clinical need.

To explore potential biomarkers of chemoprevention efficacy.	Analysis of breast tissue, urine and blood samples for potential biomarkers of chemopreventive efficacy.

### Design

A schematic overview of the trial is depicted in figure 1.

**Figure 1 F1:**
[figure not shown]
Chemoprevention in BRCA1 mutation carriers (CIBRAC) trial schema.

The crossover design allows comparison of outcomes from both treatments with the participant baseline; thus, each participant acts as their own control for both treatment arms. Blinding or masking is not achievable given the nature of administration of goserelin (subcutaneous implant). Given that each participant will receive both treatments without blinding, randomisation was felt unnecessary, and alternate allocation of treatment groups in order of recruitment is adequate. The setting of the trial in tertiary care (family history breast clinics) reflects the main location for the ongoing care and management of this cohort.

### Selection of participants

Participants will be recruited from family history breast clinics within Northern Ireland as identified by clinicians and by posters and publicity regarding the trial presented and distributed at relevant public engagement events. The participant inclusion and exclusion criteria are outlined in table 2. The chief investigator (or appropriately trained delegate) will confirm eligibility against the inclusion/exclusion criteria.

**Table 2 T2:** Inclusion and exclusion criteria

Inclusion criteria	Exclusion criteria
Age >18 years.	BRCA1 mutation of uncertain significance.
Premenopausal.	Personal history of breast or ovarian carcinoma.
Known pathogenic BRCA1 mutation.	Previous risk-reducing breast or ovarian surgery.
Intact ovaries.	Postmenopausal status.
No previous breast/ovarian carcinoma.	Concomitant use of alternative chemoprevention regimens.
No other previous malignancy.	Concomitant use of other hormonal agents less than 1 month prior to enrolment.
No previous use of chemoprevention.	Contraindications to study drug therapies.
Willingness to use non-hormonal contraception.	Contraindications to breast core biopsies.
	Pregnancy or breast feeding.
	Inability to give informed consent.
	Having made a decision to proceed with risk-reducing surgery.

### Description of interventions

#### Goserelin and anastrozole treatment

Participants will receive goserelin 3.6 mg by subcutaneous injection every 28 days for 12 weeks, simultaneously receiving oral anastrozole 1 mg per day for 12 weeks.

#### Tamoxifen treatment

Participants will receive oral tamoxifen 20 mg per day for 12 weeks.

#### Washout period

On completion of the first treatment arm, participants will have a 4-week period of no treatment to allow washout of active substances, before commencing second treatment arm.

### Description of processes

#### Procedure for obtaining informed consent and trial arm allocation

Participants will receive an adequate explanation of the objectives, methods, potential risks and anticipated benefits of the study. They will be given a current, ethically approved participant information sheet for their consideration. Following this, informed consent will be obtained once women have had a minimum of 24 hours to consider trial entry and the opportunity to ask further questions. Following consent, participants will be provided with a copy of the signed consent form, with a copy filed in the patient notes, and the original retained in the site file, available for inspection if required.

No protocol-required assessments will be conducted until the consent form has been signed and dated by both the participant and the investigator. Participants will be provided the option to allow the use of blood samples, other body fluids and tissues obtained during testing, operative procedures, or other standard medical practices for further research purposes. Participants will be alternately allocated to treatment arms.

#### Replacement of participants

In the case of a participant request for withdrawal or failure to collect biological samples, the participant will be withdrawn from the study and a new participant enrolled into the treatment arm the original participant has been retracted from.

#### Percentage consenting to trial entry

Records will be kept of all the patient information sheets distributed to allow calculation of percentage of patients consenting to trial entry.

#### Compliance measurement

Participants will receive a medication diary card for each oral treatment at the same time the tablets (anastrozole for arm A and tamoxifen for arm B) are issued to track compliance.

#### Concomitant medication

Participants must be instructed not to take any medications (including herbal and over-the-counter remedies) during the study without prior consultation with the investigator. Any hormonal treatments (including all forms of hormonal contraception) are prohibited. Concomitant medications must be recorded in the patients’ notes at the time of initial consultation and any amendments documented at subsequent visits.

#### QOL assessment

Questionnaires will be completed on day 1 (baseline), day 84 (±3 days, following the end of the first arm) and day 196 (±3 days following the end of the second arm).

Two questionnaires will be used to assess health-related QOL:European Organisation for Research and Treatment of Cancer Questionnaire to Quality of Life of Cancer patients, assessing QOL.European Organisation for Research and Treatment of Cancer Questionnaire module to assess quality of life of patients with breast cancer, assessing treatment side effects and sexual dysfunction.

#### Recording of adverse events

An adverse event (AE) is any untoward medical occurrence (including deterioration of a pre-existing medical condition) in a subject administered an investigational medicinal product (IMP). The event does not necessarily have a causal relationship with treatment or usage. An adverse reaction (AR) is an AE that is suspected as having a causal relationship to the IMP. Each AE and its causality, severity and expectedness are assessed by the chief investigator (or nominated representative) and recorded in the patient notes. All IMPs in this study are licensed with well-defined safety profiles. As such, we will only record data relating to ARs in the case report form (CRF). If the event is classified as a serious adverse event (SAE), the reporting procedures as per Belfast Health and Social Care Trust (BHSCT) will also be followed. Follow-up will continue until all the necessary safety data for the event have been gathered and until the AR or SAE has resolved, returned to baseline or stabilised.

#### Pregnancy testing

Participants will be asked to provide a non-sterile urine sample (the initial stream) in a clean, non-sterile receiver. The sample will be used to perform a urinary human chorionic gonadotropin (hCG) test in the clinic following the manufacturer’s standard operating procedure.

Pregnancy testing will be performed twice:At the time of assessment of eligibility for the trial following consent, prior to the first arm treatment commencement.On day 112±3 (week 16), prior to starting the second treatment arm.

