#### Core biopsies

Biopsy samples will be collected as standard using a 14G core biopsy needle under ultrasound guidance in the Department of Radiology at Belfast City Hospital. Two core biopsies will be sharply dissected into at least four smaller samples (approximately 5 mm^3^ each) and placed in individual Eppendorf tubes, then snap-frozen with liquid nitrogen and stored for later use. Two core biopsies will be placed in individual formalin-containing sample pots, after which they will be formalin-fixed paraffin-embedded (FFPE) as per standard operating procedures within the Belfast Trust.

Core biopsies will be taken on day 1 (baseline), day 84 (±3 days following the end of the first arm) and day 196 (±3 days following the end of the second arm).

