#### Urine samples

Urine sampling will be performed on day 1 (baseline), day 84 (±3 days following, end of the first arm) and day 196 (±3 days following, end of the second arm). Mid-stream urine samples will be collected in sterile containers. Within 2 hours of collection samples will be centrifuged to separate debris from the urine and then stored at −80°C in 500 µL aliquots in RNAse free tubes. Following sample accrual. Samples will be thawed and urinary 2-OHE_2_ and 4-OHE_2_ levels and levels of depurinating DNA adducts will be measured using UPLC-MS/MS.

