#### Whole blood sampling

Each participant will provide one whole blood sample at one time point in the study. This will be performed at baseline (day 1), unless the patient is already enrolled and receiving treatment, in which case the whole blood sampling will be performed at the end of the treatment arm that they are currently receiving (day 84±3 days or day 196±3 days).

The whole blood samples will be collected at the same venepuncture session as serum sampling. Blood will be collected into one EDTA-coated tube and frozen/stored at −80°C in 1 mL aliquots. Samples will be retained for future use including DNA extraction.

The timeframe for interventions and assessments is summarised in table 3.

**Table 3 T3:** Summary of assessments and interventions

Time point	<30 days prior to entry	Week 1	Week 4	Week 8	Week 12	Week 16	Week 20	Week 24	Week 28	Week 32 (end of trial)
Enrolment										
Informed consent	A+B									
Baseline history	A+B									
Eligibility screen and pregnancy test		A+B				A+B				
Treatment allocation		A+B								
Conmeds	A+B	A+B	A	A	A+B	A+B	B	B	A+B	A+B
Interventions										
Start tamoxifen (12 weeks)		B				A				
Start anastrozole (12 weeks)		A				B				
Goserelin implant injection		A	A	A		B	B	B		
Assessments										
Quality of life assessment		A+B			A+B				A+B	
Core breast biopsies ×3		A+B			A+B				A+B	
Blood samples for oestrogen and metabolite levels		A+B			A+B				A+B	
Blood sample for whole blood		A+B			A+B				A+B	
Urine samples for oestrogen and metabolite levels		A+B			A+B				A+B	
Adverse event assessment	A+B	A+B			A+B	A+B			A+B	A+B

A corresponds to treatment arm A of the study (goserelin and anastrozole followed by tamoxifen. B corresponds to treatment arm B, tamixofen followed by goserelin and anastrozole.

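### No pregnancy test is scheduled during or after the second course, so a pregnancy then could go undetected and that woman's day-196 values could be misattributed to the second regimen

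*Protocol article*

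**What the plan says.** The Pregnancy testing section sets a closed schedule: "Pregnancy testing will be performed twice". The first test is "At the time of assessment of eligibility for the trial following consent, prior to the first arm treatment commencement"; the second is "On day 112±3 (week 16), prior to starting the second treatment arm". In Table 3, the row "Eligibility screen and pregnancy test" is filled for both groups at week 1 and week 16 and nowhere else.

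The article treats pregnancy as relevant to the trial. Table 2 excludes "Pregnancy or breast feeding" and requires willingness to use non-hormonal contraception, and the Concomitant medication section prohibits hormonal contraception.

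On sampling, "Core biopsies will be taken on day 1 (baseline), day 84 (±3 days following the end of the first arm) and day 196". Serum, urine and questionnaires follow the same days. The Comparisons section sets each woman's end-of-arm results against her own earlier results. Table 3 schedules adverse event assessment for both groups at weeks 28 and 32.

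**The concern.** The participants are premenopausal, have intact ovaries and may not use hormonal contraception. Each woman is tested before each course, and the washout places the second test after the first course as well. The second course has no test during it, at its end or in the four weeks that follow.

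Two things are at stake. First, exposure to the second regimen in pregnancy is not checked by any scheduled test. Second, day-196 values from a woman not known to be pregnant would enter the within-woman comparison without a marker. Pregnancy can be expected to alter oestrogen-related measures, and could alter proliferation and quality of life. Group A takes tamoxifen second and group B takes goserelin plus anastrozole second, so each regimen is exposed to this in half of the women. With 12 women and descriptive summaries, one such record carries visible weight.

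**Working it through.** The plan gives no figure to reproduce: it states that no sample size calculation was made and plans only descriptive statistics. The check is therefore calendar arithmetic, followed by an illustration on assumed rates.

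**Inputs.** End-of-arm samples on days 84 and 196, each ±3 days (Core biopsies; Urine samples). Last test on day 112±3 (Pregnancy testing). Washout of 4 weeks (Washout period). End of trial at week 32 (Table 3), which is 32 × 7 = day 224. Twelve women allocated 1:1 (Abstract), so 6 per sequence.

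**Cover of each course.**

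| | First course | Second course |
|---|---|---|
| Test before the course | eligibility | day 112±3 |
| End-of-arm samples | day 84 | day 196 |
| Next scheduled test | day 112, 28 days later | none |

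- First course, samples to next test: 112 − 84 = 28 days. With the windows, (112 − 3) − (84 + 3) = 22 to (112 + 3) − (84 − 3) = 34 days.
- Second course, last test to samples: 196 − 112 = 84 days. With the windows, (196 − 3) − (112 + 3) = 78 to (196 + 3) − (112 − 3) = 90 days.
- Last test to end of trial: 224 − 112 = 112 days, half of the 224 study days. The second course is 84 of 168 treatment days, also half.

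**Weight of one case.** 1/12 = 8.3% of day-196 sets; 1/6 = 16.7% within a sequence.

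**How likely is a case?** The documents give no conception rate. Purely as an assumption, take 2% to 15% per woman-year, with P(at least one) = 1 − exp(−rate × woman-years).

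- All 12 women: 12 × 84/365.25 = 2.76 woman-years; 0.055 to 0.414 expected; P = 5.4% to 33.9%.
- Only the 6 women then on tamoxifen: 6 × 84/365.25 = 1.38 woman-years; 0.028 to 0.207 expected; P = about 3% to 19%.

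The first line overstates the risk, because the other six women are then on ovarian suppression. Both lines count any conception. Only one still unrecognised when the results are interpreted would cause misattribution, and that probability is lower again.

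**Other routes to detection.** All women have contact at weeks 28 and 32. Between weeks 16 and 28, Table 3 has no entry for group A; the week 20 and week 24 entries are for group B only. Without a test, detection rests on the woman recognising and reporting the pregnancy.

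**The case against.** The strongest reply is that the schedule is consistent and symmetric: one test before each course, with the text and Table 3 in agreement. The article nowhere calls the day-112 test a check on the first course; that is a by-product of the washout. This stands. There is no contradiction, and the documents set no standard that the second course fails. The two courses nevertheless end up with different cover, and no reason is given.

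A reader might infer that a pregnant woman's day-196 samples *would* be read as a drug effect. The documents do not support that. The pregnancy would have to remain unrecognised until interpretation. Contact continues to week 32, and serum and urine are frozen and assayed only after accrual, so it could surface first. A marked oestrogen rise on goserelin plus anastrozole would also stand out against the expected suppression; on tamoxifen it may be less conspicuous.

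A reader might also infer that a pregnancy judged unrelated to treatment would be lost, because the CRF takes only adverse reactions. But all adverse events go into the patient notes, serious ones follow the Trust's procedures, and a condensed article may leave pregnancy reporting to the full protocol. That silence is not a finding.

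Finally, the stakes are limited. The primary endpoints are consent percentage and compliance, the laboratory outcomes are exploratory, and no formal test is planned. This also stands, although day-196 quality of life belongs to the secondary tolerability endpoint.

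**Conclusion.** The point holds in a limited form. The article fixes two tests, and none falls during or after the second course, so a pregnancy then could go undetected and the woman's day-196 values could be misattributed. One case would affect 1 of 12 women overall, or 1 of 6 in her sequence. Its probability cannot be derived from the documents and is probably small; the ranges shown rest on an assumed conception rate and are upper illustrations for misattribution.

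The data affected are the exploratory laboratory measures and secondary quality of life. Nothing here biases the primary endpoints or a hypothesis test, and the sections do not conflict. This is a worthwhile, cheap improvement, not a flaw that undermines the trial.

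**What to change.** As a sample-validity measure, determine hCG status on the urine already collected at days 84 and 196. Record it in the CRF, and flag any affected woman's end-of-arm samples and questionnaires so that they are not summarised as drug effect.

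The cost is two strip tests per woman on existing urine, one CRF field and a short amendment. No new visit, staff or invasive procedure is needed.

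Separately, the sponsor and investigators should reconcile the unequal test cover of the two courses, or state why it is intended. The timing of safety testing and the handling of a positive result are theirs to decide; no schedule is proposed here.
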